#### Pilot RCT

As already outlined, the pilot RCT will not aim to assess intervention effects, but to assess the feasibility and acceptability of implementing the intervention in state secondary schools in England. Pilot primary outcomes will be meeting criteria for progression to a phase III trial comprising:The intervention is implemented with 70% fidelity in ≥ 3 of four intervention schools.Process evaluation indicates that the intervention is acceptable to 70% of students and staff involved in implementation.Randomisation occurs and ≥ 5 of six schools accept randomisation and continue within the study.Student questionnaire follow-up rates are ≥ 80% in ≥ 5 of SIX schools.Linkage of self-report and routine administrative data on pregnancies is feasible.

#### Measures to be tested as part of the pilot trial

Outcome measures and analyses that would be used in a phase III RCT will be tested in the pilot. Our current intention is that the primary outcome for a phase III trial will examine unintended teenage pregnancies via routine data on births and terminations assessed at 48 months (age 16/17). Around half of under-18 conceptions in England and Wales end in abortion [1]. Yet, while recognising that a proportion of teenage pregnancies will be intended [36], we anticipate that an outcome measure that takes into account both conceptions and terminations will provide a better indication of unintended pregnancies than a measure purely focused on terminations. This is because many unintended pregnancies will not result in termination, and rates of termination will be strongly affected by the availability of local services.

We will also assess secondary outcomes which would be assessed in a phase III RCT at 24 months. The following secondary outcome measures drawn from the Ripple and Share trials [34, 35, 37] will be assessed via self-complete paper and pen questionnaire:Self-reported pregnancy and unintended pregnancy (initiation of pregnancy for boys) and STIsAge of sexual debut, number of sexual partners, use of contraception at first and last sex and non-volitional sexEducational attainment (which is a plausible and, for scale up, critical outcome of our intervention).

The full trial will conduct exploratory analyses to examine how effects on the above outcomes are moderated by SES, gender, ethnicity and baseline risk to assess intervention impact on health inequalities. These analyses will be tested as part of the pilot.

Informed by our theory of change [27–30], we will also conduct exploratory analyses to examine the following mediators [38] using existing measures [34, 35, 39–41]:School-level social norms supportive of positive relationships and sexual healthIndividual-level sexual health knowledge and skills, contraceptive skills and access, self-efficacy, sexual competence, communication with parents, school engagement and career/educational aspirations

All of the above measures will be assessed for reliability in our pilot. We will assess reliability by reporting an intra-cluster correlation coefficients (ICC) to examine the consistency of measures from baseline to follow-up among the control group (this is a different ICC to that measuring clustering within schools) and Cronbach’s alpha statistics at baseline and follow-up for scaled outcomes. See Economic evaluation section below for economic outcomes.

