### Research questions

Is it possible to optimise Positive Choices in collaboration with NCB SEF, a secondary school and other stakeholders?Is it feasible and acceptable to implement each component of this intervention in the secondary school involved in optimisation and what refinements are suggested?In light of a pilot RCT across six schools, is progression to a phase III trial justified in terms of pre-specified criteria?Are secondary outcome and covariate measures reliable and what refinements are suggested?With what rates are schools recruited to and retained in the trial?What level of student reach does the intervention achieve?What do qualitative data suggest in terms of intervention mechanisms and refinements to programme theory and theory of change?How do contextual factors appear to influence implementation, receipt and mechanisms of action?Are any potential harms suggested and how might these be reduced?What sexual health-related activities occur in and around control schools?Are methods for economic evaluation in a phase III trial feasible

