### Study settings and population

Positive Choices will be delivered in one English state secondary school in the feasibility phase of the study. In the pilot, six English state secondary schools (including free schools and academies) will be included. Positive Choices is a universal intervention aimed at 11–16-year-olds in participating secondary schools in England. While the intervention will have effects at the whole-school level, the study population in the pilot will be students nearing the end of year 8 (age 12–13 years) at baseline who will receive the year 9 classroom curriculum. These pupils will be at the end of year 9 (age 13–14 years) at follow-up 12 months later (see below). In a phase III trial, the intervention would target students in years 9 and 10. The targeting of year 9 students in the feasibility assessment and pilot RCT phases reflects the truncated timescales of these phases. Years 9 and 10 would be targeted in a phase III RCT because proximal risk factors are manifesting [33], prevention is not too late and sex education is acceptable [34, 35]. Prior stakeholder engagement suggests provision to year 11 students is unfeasible because of GCSE exam preparation.

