#### Pilot RCT

In the pilot RCT, baseline surveys will be carried out before randomisation as students near the end of year 8 (age 12/13) in June 2018 and will collect data on pre-hypothesised outcome variables, covariates and moderators, drawing on existing survey items as outlined above. Paper questionnaires will be completed confidentially in classrooms supervised by fieldworkers, with teachers remaining at the front of the class to maintain quiet and order, but unable to see student responses. We will survey absent students by leaving questionnaires and stamped addressed envelopes with schools.

We will resurvey students at 12 months (June 2019) as students near the end of year 9 (age 13/14) and will collect self-report data on experiences of the intervention, outcomes and pre-hypothesised potential mediators. Fieldworkers will be blind to allocation. Based on past experience, [37, 42] in the pilot, we expect 95% baseline survey participation and 90% at follow-up. In the pilot, data on terminations and births at 18 months will be obtained in collaboration with the Office for National Statistics (ONS) and the Department of Health (DH) by linking data on female trial participants via the national pupil database and other identifiers to routine ONS data on registration of births and statutory termination notifications, by staff blind to allocation. Linkage of birth and termination data has been previously conducted for observational studies [33] but has not involved linkage to survey data, and hence has not examined participant consent rates, which will be a key focus for our research. Initial discussion with ONS has established that data linkage is feasible despite the limited identifiers attached to termination records and is consistent with DH guidance and data protection law.

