#### Pilot RCT

Our main analyses will determine whether criteria for progression to a phase III trial are met. Descriptive statistics on fidelity will draw on audio-recordings of training, diaries of providers and structured observations of intervention activities. Statistics on acceptability will draw on surveys of students and trained staff and interviews with staff and students. School randomisation and retention, and student follow-up will be described using a CONSORT diagram [48]. We will assess the precision of data linkage in association with ONS researchers.

Additional analyses will address our other research questions. Descriptive summaries of baseline and follow-up data by arm will be tabulated. We will assess the reliability of secondary outcome measures by reporting intra-cluster correlation coefficients (ICC) to examine the consistency of measures from baseline to follow-up (this is different from the use of ICC to measure clustering of variables within schools) and Cronbach’s alpha statistics at baseline and follow-up for scaled outcomes. We will pilot intention-to-treat analyses of outcomes [44] and moderator analyses (how effects vary by SES, gender, ethnicity and baseline risk).

Qualitative data will be subject to thematic content analysis (in vivo/axial codes; constant comparison [49] informed by realist approaches to evaluation [50] and May’s implementation theory [46] to examine potential mechanisms of action and of harm, determine how contextual factors influence implementation and mechanisms, describe relevant activities in and around intervention and control schools and refine our programme theory and theory of change.

Our economic feasibility study will pilot collection of quality of life and assess the feasibility of methods to be used within a full trial, which in line with NICE guidance, would involve a wider cost consequence analysis, comparing intervention costs with the full range of study outcomes.

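### The 12-month control-group ICC mixes true change with reporting error, so a low value cannot be read as unreliability of the behavioural outcomes

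*Protocol article*

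**What the plan says.** The Research questions ask: "Are secondary outcome and covariate measures reliable and what refinements are suggested". Under Measures to be tested as part of the pilot trial, the article lists the secondary outcomes (pregnancy, sexually transmitted infections, sexual debut, partners, contraception at first and last sex, non-volitional sex, educational attainment) and the mediators. It then says: "All of the above measures will be assessed for reliability in our pilot". Two statistics are named. One is an ICC for the "consistency of measures from baseline to follow-up among the control group". The other is Cronbach's alpha "statistics at baseline and follow-up for scaled outcomes".

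The timing is given under Assessment and follow-up, Pilot RCT: "baseline surveys will be carried out before randomisation as students near the end of year 8 (age 12/13) in June 2018", and then "We will resurvey students at 12 months (June 2019) as students near the end of year 9 (age 13/14".

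The Analyses section for the pilot RCT repeats the ICC for secondary outcomes as the "consistency of measures from baseline to follow-up (this is different from the use of ICC to measure clustering of variables within schools". The words limiting it to the control group are absent there.

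**The concern.** Test-retest agreement measures reliability only if the true value stays put between the two tests. Here the gap is a year, and the outcomes are ones that students of this age may newly experience during it. The article points the same way when it explains the choice of years for the full trial: "Years 9 and 10 would be targeted in a phase III RCT because proximal risk factors are manifesting". A student who truthfully answers no in June 2018 and yes in June 2019 lowers the ICC just as a misreport does.

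Alpha offers no second view of the behavioural outcomes, because it applies to scaled measures only. For items such as sexual debut, pregnancy or infection, which are not described as scales, the 12-month ICC is the only reliability statistic named. At stake is whether the pilot can answer its own question about which measures need refinement. A low ICC could prompt rewording of an item that students answer accurately.

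**Working it through.** **Plan's own figure.** 6 schools × about 180 students = 1,080, which matches the number under Analytic sample and proposed sample size. The article gives no ICC value or threshold to reproduce.

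**Students who supply the ICC.** There are two control schools (Comparators), about 180 students each (Randomisation), with 95% participation expected at baseline and 90% at follow-up (Assessment and follow-up). 2 × 180 × 0.95 × 0.90 = 307.8, about 308. If the 90% applies to all enrolled students, it is 2 × 180 × 0.90 = 324.

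**Cumulative yes/no item, no reporting error.** Let prevalence be p0 at baseline and p1 at follow-up. Everyone positive at baseline is still positive at follow-up, so the covariance is p0 − p0p1 = p0(1 − p1). The consistency form of the ICC is

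ICC = 2p0(1 − p1) / [p0(1 − p0) + p1(1 − p1)].

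The article gives no prevalences, so those below are assumptions chosen to show the range.

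| p0 to p1 (assumed) | Numerator | Denominator | ICC |
|---|---|---|---|
| 1% to 3% | 0.0194 | 0.0099 + 0.0291 = 0.0390 | 0.50 |
| 2% to 6% | 0.0376 | 0.0196 + 0.0564 = 0.0760 | 0.49 |
| 5% to 10% | 0.0900 | 0.0475 + 0.0900 = 0.1375 | 0.65 |
| 2% to 3% | 0.0388 | 0.0196 + 0.0291 = 0.0487 | 0.80 |
| 5% to 6% | 0.0940 | 0.0475 + 0.0564 = 0.1039 | 0.90 |

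The one-way form gives 0.49, 0.48 and 0.64 for the first three rows, so the choice of ICC hardly matters. Reporting is perfect in every row; only the amount of real change differs.

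**Scales.** With equal variances at the two surveys, expected ICC = reliability × 12-month stability of the true score. Reliability 1.0 with stability 0.5 gives 0.50, and so does reliability 0.5 with stability 1.0. The ICC alone cannot tell these apart. An assumed reliability of 0.85 with stability of 0.5 to 0.7 gives 0.85 × 0.5 = 0.43 to 0.85 × 0.7 = 0.60.

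**Precision.** In a simulation of 308 students with perfect reporting and 2% rising to 6% (about 6 and 18 positive), the central 95% of ICC estimates ran from 0.22 to 0.72. For items asked only of sexually active students, an assumed 1% to 3% active at baseline leaves 308 × 0.01 = 3.1 to 308 × 0.03 = 9.2, so about 3 to 9 students.

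**The case against.** Several points on the other side are sound, and they limit the finding.

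- **Some reliability information remains.** A reader might infer that the ICC measures change instead of reliability, or that it would grade perfectly reported items as poor. Neither follows. The ICC reflects reliability and stability together, so a high value supports reliability. With a small rise in prevalence it stays at 0.80 to 0.90, and the article sets no threshold by which anything is graded.
- **No decision rule is attached.** A reader might also infer that sound items would be dropped. The article only says the ICC will be reported. It counts this among the additional analyses, and none of the five criteria for progression to phase III depends on it.
- **Some items should not change.** Once a student has reported debut, age at debut and contraception at first sex are fixed facts. Disagreement on them is reporting error, which the two surveys can show. The difficulty there is small numbers, not real change.
- **The two descriptions do not clearly conflict.** A reader might take the Analyses section to pool both arms and so bring in intervention-driven change. It does not say so. It is a shorter restatement that omits the control-group limit, and the fuller description is explicit. The wording needs aligning.
- **Alpha is already planned** at both surveys for scales and is computed within each one, although it measures internal consistency only.

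What these points do not answer is that, for behavioural items whose true value can change over the year, the only named reliability statistic cannot separate that change from error.

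**Conclusion.** The concern holds in a limited form. The 12-month control-group ICC confounds true change with measurement error and may understate the reliability of accurately reported cumulative items. Under perfect reporting the illustrated values run from about 0.5 to 0.90, depending only on how much prevalence rises. A low value is therefore uninterpretable as it stands; a high one is reassuring.

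The size rests on prevalences the article does not give, and on reading the behavioural outcomes as single items, which it implies but does not state. The consequence is confined to the reliability research question and the refinement of measures. Progression to phase III is not affected. The change is still worth making, because it costs little and alters what the pilot can conclude about its main behavioural measures.

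**What to change.** 1. Report the 12-month ICC as stability, not as a test of reliability.
2. State the control-group limit in the Analyses section, as under Measures to be tested as part of the pilot trial.
3. Judge reliability of the *ever* items by logical consistency between the surveys: the number and proportion reporting *ever* at baseline and *never* at follow-up. Among students already reporting debut at baseline, also give the number whose age at debut or contraception at first sex changes.
4. Give numerators and denominators for each check, since perhaps only 3 to 9 control students will contribute (1% to 3% of about 308, assumed).
5. Keep Cronbach's alpha at each survey for scales.

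The cost is some rewording and a few tabulations of data already being collected, with no extra survey. There are two downsides. The pilot would claim no test-retest reliability figure. The logical checks also miss a student who misreports the same way both times.

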### Assessment and follow-up

#### Feasibility assessment phase

A baseline needs survey of students approaching the end of year 8 will be undertaken. Other data collected in the feasibility phase are described below under ‘Process evaluation’.

#### Pilot RCT

In the pilot RCT, baseline surveys will be carried out before randomisation as students near the end of year 8 (age 12/13) in June 2018 and will collect data on pre-hypothesised outcome variables, covariates and moderators, drawing on existing survey items as outlined above. Paper questionnaires will be completed confidentially in classrooms supervised by fieldworkers, with teachers remaining at the front of the class to maintain quiet and order, but unable to see student responses. We will survey absent students by leaving questionnaires and stamped addressed envelopes with schools.

We will resurvey students at 12 months (June 2019) as students near the end of year 9 (age 13/14) and will collect self-report data on experiences of the intervention, outcomes and pre-hypothesised potential mediators. Fieldworkers will be blind to allocation. Based on past experience, [37, 42] in the pilot, we expect 95% baseline survey participation and 90% at follow-up. In the pilot, data on terminations and births at 18 months will be obtained in collaboration with the Office for National Statistics (ONS) and the Department of Health (DH) by linking data on female trial participants via the national pupil database and other identifiers to routine ONS data on registration of births and statutory termination notifications, by staff blind to allocation. Linkage of birth and termination data has been previously conducted for observational studies [33] but has not involved linkage to survey data, and hence has not examined participant consent rates, which will be a key focus for our research. Initial discussion with ONS has established that data linkage is feasible despite the limited identifiers attached to termination records and is consistent with DH guidance and data protection law.

### Analytic sample and proposed sample size

Feasibility assessment will be carried out in one London school. Involving only one school at this stage enables intensive engagement while assessing that intervention activities are in principle feasible. The survey will involve approximately 180 year-9 students but note that this is undertaken to assess the feasibility of this as an intervention component only. Evaluation activities (see below for details) in this feasibility phase will involve small samples intended to contribute to assessing feasibility in principle rather than providing statistically representative findings. Qualitative research will involve purposive samples aiming to encompass diversity on key criteria.

Six schools varying by local level of deprivation and school-level GCSE attainment will be recruited to the pilot. No power calculation for this phase has been conducted since the aim of this phase is to assess progression criteria in a pragmatic, relatively small but purposively diverse sample of schools prior to a future phase III RCT which would involve a larger sample in order to examine intervention effects informed by a formal power calculation. Approximately 1080 students will be surveyed in the pilot at the end of year 8 (age 12/13) at baseline and followed-up 12 months later. While no power calculation for this phase has been undertaken, previous similar studies suggest this sample will be sufficient in order to assess student response rates, the reliability of measures and intervention reach [42, 43]. Evaluation activities (see below for details) in this feasibility phase will involve samples intended to contribute to assessing local feasibility rather than providing statistically representative findings. Qualitative research will involve purposive samples aiming to encompass diversity on key criteria.

### Protection against bias

Although the aim of this study is to optimise the intervention, assess feasibility and then pilot outcome measures and analyses rather than estimate intervention effects, we will pilot methods aimed at minimising bias. The investigator team and the intervention delivery team will be separately managed. In the pilot RCT, outcome data will be collected and analysed blind to allocation, and we will examine effects adjusting for potential baseline confounders (age, gender, SES and ethnicity). We will aim to maximise response rates at each pilot RCT site at baseline and follow-up to minimise non-response and attrition bias, for example, following up those individuals not present during survey sessions. Response rates and qualitative data will be analysed to refine data collection methods prior to a phase III trial examining effectiveness. Blinding of participants to allocation is not possible.

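### The covariates named for the piloted effect analyses leave out the student's baseline value of the measure, which gives up some precision for scale-type survey measures (minor)

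*Protocol article*

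**What the plan says.** All references are to the protocol article.

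- *Protection against bias* gives the only covariate list for effect estimates: "we will examine effects adjusting for potential baseline confounders (age, gender, SES and ethnicity".
- *Assessment and follow-up, Pilot RCT* says that the June 2018 survey, done before randomisation, "will collect data on pre-hypothesised outcome variables, covariates and moderators".
- *Measures to be tested as part of the pilot trial* plans, for all listed measures, to "examine the consistency of measures from baseline to follow-up among the control group". This implies that each is measured at both times.
- *Analyses, Pilot RCT* says "We will pilot intention-to-treat analyses of outcomes", with no covariate list. It gives baseline risk a role only in "moderator analyses (how effects vary by SES, gender, ethnicity and baseline risk".
- On purpose, *Endpoints of the study, Pilot RCT* says "the pilot RCT will not aim to assess intervention effects", while the measures section says "Outcome measures and analyses that would be used in a phase III RCT will be tested in the pilot".

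**The concern.** A student's own baseline value is usually the best single predictor of the same measure a year later, and it addresses baseline differences between schools directly. Gender, SES and ethnicity do so only indirectly, and age varies little within one school year. Schools are recruited to differ in deprivation and GCSE attainment and are then split four to two, so arms that differ at baseline are to be expected. The data that would deal with this are collected anyway, but the named adjustment set does not use them. If this model is carried into phase III unchanged, the survey measures there would be analysed less precisely than the data allow.

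**Working it through.** **The plan's own figure.** 6 schools × 180 students = 1080, as stated under *Analytic sample and proposed sample size*. No power, effect size, school ICC or baseline-to-follow-up correlation is given, so everything below rests on assumed ranges.

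**Inputs.** Four intervention and two control schools, so the arm-difference factor is 1/4 + 1/2 = 0.75. Expected participation is 95% at baseline and 90% at follow-up. Students per school: 180 × 0.95 × 0.90 ≈ 154 if the 90% applies to those surveyed at baseline, or 180 × 0.90 = 162 if it applies to the year group. Assumed: school ICC 0.01 to 0.05; student-level correlation r of 0.4 to 0.7 for scales.

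**1. Student-level residual variance.** Remaining fraction = 1 − r².
- r = 0.4: 1 − 0.16 = 0.84, a fall of 16%.
- r = 0.7: 1 − 0.49 = 0.51, a fall of 49%.

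These figures take no account of variance that the demographics already explain.

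**2. Chance baseline difference between arms.** SD = √{[ICC + (1 − ICC)/m] × 0.75}, in outcome SDs, with m = 154.
- ICC 0.01: √[(0.01 + 0.00643) × 0.75] = 0.111.
- ICC 0.05: √[(0.05 + 0.00617) × 0.75] = 0.205.

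With m = 162 the values are 0.110 and 0.205. Only the part that persists to follow-up enters the effect estimate.

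**3. Variance of the arm difference with six schools.** This is proportional to ICC × (1 − r_school²) + (1 − ICC) × (1 − r_student²)/m. With m = 162 and r_student = 0.7, the reduction is:

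| r_school | ICC 0.01 | ICC 0.05 |
|---|---|---|
| 0 | 18.6% | 5.1% |
| 0.7 | 49.0% | 49.0% |
| 0.8 | 58.3% | 62.4% |

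First row, ICC 0.01: (0.99 × 0.49/162)/(0.01 + 0.99/162) = 0.00299/0.01611 = 18.6%. ICC 0.05: (0.95 × 0.49/162)/(0.05 + 0.95/162) = 0.00287/0.05586 = 5.1%. The student-level percentages in step 1 therefore carry over to the trial estimate only if the schools' own means are similarly correlated over time.

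**4. Degrees of freedom.** A cluster-level analysis that spends one degree of freedom on the school-mean baseline moves from t = 2.776 (4 df) to t = 3.182 (3 df). The interval narrows only if r_school exceeds √[1 − (2.776/3.182)²] ≈ 0.49. This applies to a school-mean covariate; the covariate recommended here is the student's own value.

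**5. Rare binary items.** For an item of the ever/never type, the largest possible correlation is √{p0(1 − p1)/[p1(1 − p0)]}, where p0 and p1 are the baseline and follow-up prevalences.
- Assumed 1% then 5%: 0.438, at most 19% of variance.
- Assumed 5% then 15%: 0.546, at most 30% of variance.

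These are ceilings. They would rest on about 0.01 × 154 ≈ 1.5 to 0.05 × 154 ≈ 8 baseline-positive students per school, too few for a stable term.

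**The case against.** Four objections carry weight.

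*The list may not be exhaustive.* It stands in a bias section, does not say that nothing else will be used, and comes without a model. A reader might infer a closed set that rules out the baseline value; the text does not say so, and an analysis plan that is not shown could add the term. This stands against any claim of a prohibition. It does not remove the point: four covariates are named without any sign that they are examples, and the most useful one for scales is absent.

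*Most listed outcomes would gain little.* Pregnancy, STIs and sexual behaviour are presumably rare at age 12/13, contraception at first or last sex is undefined for students who have not had sex, and no baseline for attainment is described. This stands. The gain lies mainly with the exploratory mediators and CHU-9D. Even there, the survey description names mediators explicitly only at follow-up; their baseline is inferred from the reliability plan. Baseline CHU-9D is mentioned with reference to a full trial.

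*The intended phase III primary outcome is not affected.* It is "unintended teenage pregnancies via routine data on births and terminations assessed at 48 months". No baseline linkage is described, and a value at age 12/13 would be almost constant. A reader might infer that the main phase III comparison is weakened; the documents do not support that.

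*No pilot decision depends on it.* The progression criteria are fidelity, acceptability, randomisation and retention, follow-up rates and linkage. None uses an effect estimate. This stands and sets the severity.

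**Conclusion.** The point holds as a minor one. The named covariates omit the baseline value of the measure although the plan collects it before randomisation. For scale or continuous survey measures with an informative baseline, that gives up precision and some control of chance differences between four and two schools. The size is 16% to 49% of student-level residual variance if r is 0.4 to 0.7, against a chance baseline difference with an SD of 0.11 to 0.21 if the school ICC is 0.01 to 0.05. All of these correlations and ICCs are assumptions. The gain in the six-school estimate could be much smaller or somewhat larger, depending on the school-level correlation. No conclusion of the pilot is put at risk. The point matters for the piloted estimates and because the pilot tests the analyses meant for phase III.

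**What to change.** Amend the sentence in *Protection against bias* so that each scale or continuous survey measure is also adjusted for the student's own baseline value of that measure, in addition to the covariates already named. Add a missing-indicator so that students with follow-up data only are kept; at 95% baseline participation about 180 × 0.05 = 9 students per school would lack a baseline value. Keep the demographic set alone for items that are near zero or undefined at baseline and for the linked births and terminations outcome.

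The cost is one sentence and one model term (plus its indicator) per measure, with no new data collection where the measure is already in the baseline survey. The planned baseline-to-follow-up consistency figures in the control group will show for which measures the term is worth carrying into phase III.
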